# Simulation-Based Education for Staff Managing Aggression and Externalizing Behaviors in Children With Autism Spectrum Disorder in the Hospital Setting: Pilot and Feasibility Study Protocol for a Cluster Randomized Controlled Trial

**DOI:** 10.2196/18105

**Published:** 2020-06-04

**Keywords:** feasibility studies, autism spectrum disorder, intellectual disability, high-fidelity simulation training, pediatric nursing, child, adolescent, aggression

## Abstract

**Background:**

Children with autism spectrum disorder (ASD) frequently demonstrate aggression and externalizing behaviors in the acute care hospital environment. Pediatric acute care nursing staff are often not trained in managing aggression and, in particular, lack confidence in preventing and managing externalizing behaviors in children with ASD. High-fidelity simulation exercises will be used in this study to provide deliberate practice for acute care pediatric nursing staff in the management of aggressive and externalizing behaviors.

**Objective:**

The purpose of this study is to conduct a pilot and feasibility cluster randomized controlled trial (RCT) to evaluate the effectiveness of simulation-based education for staff in managing aggression and externalizing behaviors of children with ASD in the hospital setting.

**Methods:**

This study has a mixed design, with between-group and within-participant comparisons to explore the acceptability and feasibility of delivering a large-scale cluster RCT. The trial process, including recruitment, completion rates, contamination, and completion of outcome measures, will be assessed and reported as percentages. This study will assess the acceptability of the simulation-based training format for two scenarios involving an adolescent with autism, with or without intellectual disability, who displays aggressive and externalizing behaviors and the resulting change in confidence in managing clinical aggression. Two pediatric wards of similar size and patient complexity will be selected to participate in the study; they will be randomized to receive either simulation-based education plus web-based educational materials or the web-based educational materials only. Change in confidence will be assessed using pre- and posttraining surveys for bedside nursing staff exposed to the training and the control group who will receive the web-based training materials. Knowledge retention 3 months posttraining, as well as continued confidence and exposure to clinical aggression, will be assessed via surveys. Changes in confidence and competence will be compared statistically with the chi-square test using before-and-after data to compare the proportion of those who have high confidence between the two arms at baseline and at follow-up. The simulation-based education will be recorded with trained assessors reviewing participants’ abilities to de-escalate aggressive behaviors using a validated tool. This data will be analyzed using mean values and SDs to understand the variation in performance of individuals who undertake the training. Data from each participating ward will be collected during each shift for the duration of the study to assess the number of aggressive incidents and successful de-escalation for patients with ASD. Total change in Code Grey activations will also be assessed, with both datasets analyzed using descriptive statistics.

**Results:**

This study gained ethical approval from The Royal Children's Hospital Melbourne Human Research Ethics Committee (HREC) on November 1, 2019 (HREC reference number: 56684). Data collection was completed in February 2020. Data analysis is due to commence with results anticipated by August 2020.

**Conclusions:**

We hypothesize that this study is feasible to be conducted as a cluster RCT and that simulation-based training will be acceptable for acute care pediatric nurses. We anticipate that the intervention ward will have increased confidence in managing clinical aggression in children with ASD immediately and up to 3 months posttraining.

**Trial Registration:**

Australian New Zealand Clinical Trials Registry (ANZCTR) ACTRN12620000139976; http://www.ANZCTR.org.au/ACTRN12620000139976.aspx

**International Registered Report Identifier (IRRID):**

DERR1-10.2196/18105

## Introduction

### Background and Rationale

Autism spectrum disorder (ASD), a neurodevelopmental disorder identified in childhood, is characterized by persistent deficits in social communication and social interaction across multiple contexts and restricted, repetitive patterns of behavior or interests [1]. Children diagnosed with ASD, with or without an intellectual disability, have an increased risk of hospitalization [2-5]. They also have longer and more frequent outpatient visits and medications prescribed than children in general [6]. Intellectual disability, one of the most prevalent comorbidities occurring in approximately 40%-70% of individuals with ASD [7-9], has been associated with greater autism symptomology with increased difficulties in communication and social functioning [10].

Exposure to the hospital environment can provide a sensory overload to children with ASD as it is often noisy and brightly lit, with people moving quickly, many unfamiliar people, and long wait times [11]. The surroundings are unfamiliar and usual home routines are not able to be maintained. The hospital environment necessitates that children must communicate with many more people, mostly unfamiliar, than usual. This is particularly challenging and stressful for children with ASD as they innately prefer less social interaction and have more difficulty identifying social cues and understanding the expressed emotions of others. Externalizing behaviors are common in children with ASD when exposed to these stressors and can result in difficult or delayed treatment, increased anxiety for the parent and child, prolonged procedure times, increased health care costs, and poorer health outcomes [2,6,11,12].

The Code Grey procedure is one of a series of emergency response codes used in some Australian hospitals. Code Grey refers to *unarmed aggression* and is called when an individual fails to respond to initial defusing mechanisms undertaken by staff [13]. At The Royal Children’s Hospital (RCH) Melbourne, the numbers of Code Grey activations are rising each year. In 2016, there were 611 recorded Code Grey activations, 1050 in 2018, and 1682 in 2019. In 2016-2017, 36% of Code Grey activations were due to aggression demonstrated by children and young people with ASD, with or without an intellectual disability [14].

### Need for a Trial

Staff training programs designed to teach best practice principles in the management of clinical aggression in pediatric acute care settings is warranted; however, evidence on training effects in general hospital settings is scant [15]. There are a number of reviews of aggression management training programs in psychiatric and mental health settings [16,17]; however, the results cannot be generalized to the acute setting or further extrapolated to the pediatric setting due to the different types of care provided in each facility and prior training of staff [18,19]. In addition, aggression management training programs designed for nursing staff working with children with neurodisabilities are rarely described in the literature. Simulation training may be an effective educational tool to practice de-escalation skills in a high-fidelity situation. Simulation-based education for communication skills has been shown to improve patient safety in a number of studies [20-22]. There is a paucity of literature in the use of simulation-based education to teach de-escalation communication techniques to staff working with children and young people, particularly those with ASD, in the acute care setting.

### Choice of Comparator

A purpose-designed and purpose-built web-based learning package for working with children and young people with ASD and aggression or externalizing behaviors was chosen as the comparator. An online learning package was chosen as it is convenient and flexible in time to complete, yet provides consistent information and allows self-paced learning. The online resource includes an opportunity for learner-determined revision of concepts, promotion of active and independent learning, and ability to link to and explore relevant resources.

### Study Purpose and Trial Design

The purpose of this study is to conduct a pilot and feasibility cluster randomized controlled trial (RCT) to evaluate the effectiveness of simulation-based education for staff in managing aggression and externalizing behaviors of children with ASD in the hospital setting.

This study has a mixed design, with between-group and within-participant comparisons to explore the acceptability and feasibility of delivering a large-scale cluster RCT and to assess trial processes, including recruitment, completion rates, contamination, and outcome measures. Randomization of two hospital wards will be performed with 1:1 sample size per cluster.

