### Summary

In summary, the aim of this study is to conduct a pilot and feasibility cluster RCT to evaluate the effectiveness of simulation-based education for acute care hospital staff in managing aggression and externalizing behaviors of children with ASD. We hypothesize that a multisite cluster RCT to evaluate this training format is feasible.

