## Methods

### Participants, Interventions, and Outcomes

#### Study Setting

The study setting is a tertiary pediatric hospital, the RCH Melbourne, Australia. Recruitment will be performed from nursing staff from one general medical ward and one general surgical ward, both of similar size and patient complexity. Hospital data indicate that children and young people with autism, with or without intellectual disability, are admitted with similar frequency to these wards. The two included wards also experience similar numbers of aggressive incidents per year requiring a hospital Code Grey response.

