#### Sample Size

We plan to recruit 10 staff members to each arm of the study. This sample size, based on our experiences in an earlier study we conducted, is a good size for a pilot and feasibility study to assess recruitment, contamination, and data collection.

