### Assignment of Groups

#### Allocation

A researcher who is not associated with this study and is not based at the study site will use a coin toss to randomize the wards included in the study to either the training intervention or the comparison group. This will occur once recruitment is complete. The first coin toss will identify which ward is being considered (ie, heads for one ward and tails for the other). The second coin toss will decide whether the selected ward is assigned to the intervention arm or to the comparator arm. Once the wards have been allocated, the study investigator will be unblinded and will individually notify participants via email regarding the arm of the study to which they have been allocated.

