#### Statistical Methods

##### Primary Outcomes

Percentages will be calculated to estimate recruitment, retention, outcomes, survey response rate, focus group participation, and the precision of those estimates. We will treat the Likert-scale scores as categories and dichotomize the 11- and 5-point scale responses. Changes in confidence and competence will be compared statistically with a chi-square test using before-and-after data to compare the proportion of those who have high confidence between the two arms at baseline and at follow-up.

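### The between-arm chi-square test of nurse confidence cannot separate training from ward, because each arm is a single ward

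*Protocol article*

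**What the plan says.** Study Purpose and Trial Design fixes the design: "Randomization of two hospital wards will be performed with 1:1 sample size per cluster". Study Setting identifies the wards as "one general medical ward and one general surgical ward" and describes them as alike in size, patient complexity, frequency of autism admissions and Code Grey numbers. Under Allocation, an outside researcher "will use a coin toss to randomize the wards included in the study to either the training intervention or the comparison group", after recruitment is complete. Sample Size states "We plan to recruit 10 staff members to each arm of the study", so all 10 nurses in an arm come from one ward. No effect size, power or intracluster correlation (ICC) is given; the number rests on experience from an earlier study.

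The analysis rule is under Statistical Methods, Primary Outcomes: "Changes in confidence and competence will be compared statistically with a chi-square test using before-and-after data". The proportions with high confidence in the two arms are compared at baseline and at follow-up. The Abstract repeats this rule. Neither place gives an allowance or caveat for ward.

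The Summary states the aim of the pilot as "to evaluate the effectiveness of simulation-based education for acute care hospital staff". The Abstract's Objective and Study Purpose and Trial Design use similar wording.

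**The concern.** The ward is the unit of randomization, and there is one per arm. The chi-square test treats 20 nurses from two wards as 20 independently randomized people. Any difference between the wards in specialty, staffing, culture or prior exposure to aggression sits inside the arm comparison and cannot be taken out of it.

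At stake is how the only planned between-arm significance test would be read. It is listed with the primary outcomes, and the Abstract's conclusions anticipate a gain in confidence on the intervention ward. A small p-value could be taken as early evidence that simulation works and carried into the case for a large cluster trial, when the design cannot support that reading.

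**Working it through.** The protocol gives no power calculation, so there is none to reproduce. The check covers what the design can estimate, what the test needs for significance, and how its error rate behaves.

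**Inputs.** From the protocol: 2 wards, 1 per arm; 10 nurses per ward; chi-square test on a dichotomized confidence score. Assumed, because the protocol does not state them: two-sided 5% level, 50% of nurses highly confident, ICC of 0.01 to 0.20, and a test with or without Yates correction.

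**1. What the design can estimate.**
- Degrees of freedom between wards within arms = wards − arms = 2 − 2 = 0. Ward variance cannot be estimated, so a mixed model, GEE or design-effect correction has nothing to estimate it from.
- A ward-level randomization test with k wards per arm has a smallest two-sided p of 2/C(2k, k). For k = 1 this is 2/2 = 1.0. For k = 3 it is 2/20 = 0.10, and for k = 4 it is 2/70 = 0.029. A p-value below 0.05 first becomes possible at 4 wards per arm.

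**2. What the nurse-level test needs for significance.** All 2×2 tables with 10 per arm were enumerated.
- Uncorrected: the smallest significant gap is 4 nurses, and only at the extremes (0 vs 4, or 6 vs 10). In mid-range it is 5 (3 vs 8, p = 0.025; 3 vs 7 gives p = 0.074).
- Yates: the smallest significant gap is 5, again at the extremes (0 vs 5, p = 0.039). In mid-range it is 6 (3 vs 9, p = 0.023; 3 vs 8 gives p = 0.072).

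**3. True type I error with no training effect.** Counts in each ward are beta-binomial with the stated ICC. The design effect is 1 + (10 − 1) × ICC.

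| ICC (assumed) | Design effect | Uncorrected | Yates |
|---|---|---|---|
| 0.01 | 1.09 | 5.2% | 1.7% |
| 0.05 | 1.45 | 9.7% | 4.1% |
| 0.10 | 1.90 | 15.5% | 8.0% |
| 0.20 | 2.80 | 26.4% | 16.9% |

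At ICC 0 the rates are 4.2% and 1.3%. If 80% of nurses were highly confident, the Yates rates would be 1.1%, 2.7%, 5.3% and 11.4%.

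**4. A fixed ward difference and no training effect.** With true proportions of 40% and 60%, the uncorrected test is significant in 12.9% of trials. With 30% and 70% it is significant in 41.8%.

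**5. The baseline test as a safeguard.** If the wards truly differed at baseline by 30% vs 60%, the uncorrected test would be significant only 24.8% of the time. A non-significant baseline result therefore says little about comparability.

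**The case against.** The strongest reply is that this is a pilot and nothing in it is decided by this test. That is largely right. The criteria under Outcomes in Study Objectives are thresholds for recruitment, attrition, acceptability, data capture and contamination. The secondary confidence criterion is 80% of participants reporting an increase, which is not a between-arm p-value. Code Grey, ward aggression and de-escalation scores are descriptive. One ward per arm is acceptable for those purposes. This lowers the severity, but it does not make the planned test interpretable.

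A second reply is that the wards were chosen as similar and that confidence is also compared at baseline. Both help a little. The stated similarity does not extend to nurse confidence, the baseline test has little power, and neither covers changes specific to one ward during follow-up.

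A third reply is that the inflation figures depend on unstated choices. This stands. With Yates correction and an ICC up to 0.05, the error rate does not exceed 5%. The confounding argument needs none of these figures.

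Three stronger readings are tempting, and the document does not support them:
- A reader might infer that any ward difference would be declared a training effect. At 10 per arm only large gaps reach significance.
- A reader might infer that the pilot claims to establish efficacy. The effectiveness wording is attached to a pilot and feasibility trial, and the Summary's hypothesis is that a multisite trial is feasible.
- A reader might fault the pilot for being unable to supply an ICC for the main trial. The protocol never says that it will.

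**Conclusion.** The test is wrong as written, at a severity below must-fix. This is a rule the protocol states, not a detail left to an analysis plan. With one ward per arm, a significant chi-square result cannot be attributed to training rather than ward, and no analysis of these two wards can change that. This conclusion needs no assumption beyond the stated design.

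The size of the error-rate problem does rest on assumptions. For an ICC of 0.01 to 0.20 and 50% high confidence, the true type I error runs from 5.2% to 26.4% uncorrected and from 1.7% to 16.9% with Yates correction. The feasibility and acceptability results, which are the primary objective, stand as planned.

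**What to change.** In Statistical Methods, Primary Outcomes, and in the matching Abstract text:

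- Replace the between-arm chi-square test with descriptive reporting of confidence by ward at each time point, including change within nurses, and with no between-arm p-value.
- State that the difference between arms is confounded with ward and is not an estimate of the training effect.
- Record this as a change made before analysis. The protocol reports data collection as complete and analysis as not yet begun.
- In the Abstract's Objective, Study Purpose and Trial Design, and Summary, reword the effectiveness aim as assessing feasibility and acceptability.

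The cost is the loss of one prespecified p-value and the need to document an amendment where Protocol Amendments anticipates none. No new data are needed.

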### Study Objectives

#### Primary Objective

The study objectives are to conduct a pilot and feasibility study and assess features of the acceptability and feasibility of our pilot design.

##### Population, Intervention, and Comparator

Our study population will include clinical nurses working in an acute care pediatric hospital. The study intervention will be comprised of simulation-based education plus web-based education resources on the management of clinical aggression and externalizing behaviors in children with ASD, with or without an intellectual disability. The study comparator will be web-based educational materials on the management of clinical aggression and externalizing behaviors in children with autism.

##### Outcomes

The following criteria will have to be met to indicate that an RCT is feasible and acceptable as planned:

Randomization: more than 10% recruitment rate from ward staff. A total of 160 staff members from the two selected wards will be eligible to participate in the study. We aim to recruit 10 staff members to each arm of the study.Completion: less than 20% attrition rate with survey completion rate of at least 80%; focus group participation rate of at least 50% of total participants.Acceptability: high acceptability of the intervention among participants as indicated by 80% of scores being 4 (good) out of 5 or higher in survey data.Data collection: follow-up survey response rate of at least 30% with acceptability and confidence levels maintained; ward data-collection rate of at least 80% of total shifts during study time in each ward.Low contamination from intervention participants as evidenced by participant report.

#### Secondary Objectives

The secondary objectives and their outcomes are as follows:

Confidence and competence: 80% of participants reporting increased confidence levels and positive qualitative comments.Data collection: 80% reporting of the number of Code Grey activations and the number of successful de-escalation episodes not requiring a Code Grey activation with description of context and outcome for each incident; participant use of de-escalation skills during simulations using the English Modified version of the De-escalating Aggressive Behaviour Scale (EMDABS).

### Summary

In summary, the aim of this study is to conduct a pilot and feasibility cluster RCT to evaluate the effectiveness of simulation-based education for acute care hospital staff in managing aggression and externalizing behaviors of children with ASD. We hypothesize that a multisite cluster RCT to evaluate this training format is feasible.

## Methods

### Participants, Interventions, and Outcomes

#### Study Setting

The study setting is a tertiary pediatric hospital, the RCH Melbourne, Australia. Recruitment will be performed from nursing staff from one general medical ward and one general surgical ward, both of similar size and patient complexity. Hospital data indicate that children and young people with autism, with or without intellectual disability, are admitted with similar frequency to these wards. The two included wards also experience similar numbers of aggressive incidents per year requiring a hospital Code Grey response.

#### Eligibility Criteria

Clinical nurses who work in the general medical and surgical wards will be invited to participate in the study. Eligible nurses will be those who are responsible for providing direct clinical care for ward patients. Nurses from these wards are excluded if they are not responsible for direct patient care (eg, care coordinators, advanced practice nurses, and nurses in charge of the shift).

#### Interventions

##### Overview

The training intervention will consist of two components:

A web-based learning package, developed using Articulate software (Articulate Global), for the management of aggression and externalizing behaviors in children and young people with autism, with or without intellectual disability, in the hospital setting as prereading.Prereading will be followed by a 1.5-hour simulation-based group education session to manage aggression and externalizing behaviors in an adolescent with autism; this will include two separate simulation exercises, each followed by a facilitated reflective debrief, which explores what the participants did well, what the challenges were, and what they will do differently next time. The first scenario involves an adolescent with autism and aggressive and externalizing behaviors. The second scenario increases in complexity and involves a nonverbal adolescent who has autism and intellectual disability who also demonstrates aggressive and externalizing behaviors. The training will be conducted in the Simulation Centre, conducted by the Simulation Faculty and Code Grey Coordinator, with an actor playing the role of the patient. The parent role in each of the scenarios will be played by a member of the Simulation Faculty. The simulation exercises will be recorded using Sportstec (also known as Studiocode) software.

